**Primary Outcomes**														
	Caregivers’ knowledge			Ratio			Continuous			Change in knowledge scores			*t* test	
	Caregivers’ attitudes			Ratio			Continuous			Change in attitudes scores			*t* test	
	Caregivers’ practices			Ratio			Continuous			Change in practices scores			*t* test	
**Secondary Outcomes**														
	**Child growth at 3 and 6 months**													
		Weight	Ratio			Continuous			Change in weight			*t* test		
		Height/Length	Ratio			Continuous			Change in height/length			*t* test		
		Weight-for-height *z* score	Ratio			Continuous			Change in weight-for-height			ANOVA^a^		
	**Child morbidity at 3 and 6 months**													
		Diarrhea	Nominal			Categorical			% of children with diarrhea			Risk ratio		
		Fever	Nominal			Categorical			% of children with fever			Risk ratio		
		Cough	Nominal			Categorical			% of children with cough			Risk ratio		

^a^ANOVA: analysis of variance.

### Data Collection Tools and Procedures

#### Data Collection Plan

Application of baseline tools and procedures will be repeated by the field staff who participated in baseline data collection to collect data from both arms. Before the data collection, a 1-day refresher training session will be organized for the 8 data collectors and 2 field supervisors. Recruitment of field staff was on the basis of proficiency in French, English, and Fulfulde (the dialect of the Mbororo people), familiarity with the Mbororo culture, and prior experience with surveys.

#### Caregivers’ Interviews

Face-to-face interviews will be conducted by trained data collectors (interviewers) using pretested interviewer-administered questionnaires. The interviewer-administered questionnaires were adapted from the UNICEF (The United Nations Children's Fund) multiple indicator cluster surveys tool [18]. The adapted questionnaire was prepared in English and then translated and back-translated into French and Fulfulde. The components of the questionnaire are household and caregiver’s sociodemographic characteristics, child demographic and health status characteristics, complementary feeding practices, and WASH facility and practices. Based on the health belief model constructs, the questionnaire contains 4 questions on caregiver’s perception of child susceptibility to malnutrition, 4 questions on caregiver’s perception of the severity of child malnutrition, 6 questions on caregiver’s perception about barriers to practicing appropriate complementary feeding and WASH, 4 questions on caregiver’s perceived benefits of appropriate complementary feeding and WASH practices, and 4 questions on caregiver’s self-efficacy to implement recommended actions. Each interview is estimated to last between 50 to 60 minutes and will be conducted according to the time, day, venue, and language convenient to the interviewee. The interviewers will read out the questions to the respondents and complete the questionnaires accordingly.

#### Anthropometric Measurements

Pretested portable anthropometry tools (battery-powered digital infant and toddler weighing scales, stadiometers, measuring tape, and lying wooden boards) will be used. The weight and height/length measurements will be performed using standard procedures [19]. Lying or sitting weights for children aged 0-23 months will be measured to the nearest 0.01 kg, and standing weights for older children will be measured to the nearest 0.1 kg. The weighing scale will be calibrated to 0 before each measurement. Recumbent lengths for children aged 0-23 months will be measured to the nearest 0.1 cm with measuring tape and lying boards placed on a flat ground surface. Standing heights for older children will be measured to the nearest 0.1 cm, with the head, shoulder, buttock, and heel touching the vertical surface of the stadiometer. Measurements will be taken twice and the mean recorded.

### Data Analysis Plan

Like the procedure at baseline, 1 biostatistician and 2 trained data entry clerks will be responsible for the endline data management and analysis. Data will be cross-checked for inconsistencies (outliers and extreme points) and errors and incompleteness before, during, and after manual entry into SPSS version 23 (IBM Corp). The data will be further treated for reverse coding, potential points, and outliers, as well as missing data, before being exported to SmartPLS2 for further investigation and fitting of the structural model.

Sociodemographic and child morbidity data will be analyzed and summarized using descriptive statistics. The data will be expressed as mean (SD) or median (range) for continuous variables and as a number (percentages) for categorical variables. The *t* test and analysis of variance for comparing group means will be used for primary and secondary outcome variables. A chi-square test will be applied to analyze the categorized variables. Child nutrition outcomes will be computed from anthropometric indices using Stata version 11 (StataCorp) and compared with the WHO 2006 growth standard median [20].

Results for group comparisons will be expressed as a risk ratio for binary outcomes, corresponding to 2-sided 95% CIs, and associated *P* values. *P* values will be adjusted to 2 decimal places with values less than .01 reported as <.01. Adjusted analyses using baseline variables will be performed using multivariate logistic regression to determine the continuing influence of key baseline characteristics on the outcomes. The Kaplan-Meier survival analysis will be used for timed variables like morbidity. Intention-to-treat analysis will be used, and the clustering effect will be considered in the analysis. All analyses will be performed at a 95% CI. The significance level will be set at a *P* value <.05.

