**Methods:**

A two-arm cluster randomized controlled trial will be conducted in the Foumban Health District and Galim Health District. The intervention and control arms will each comprise 5 clusters with 121 child–caregiver pairs. Participants in the intervention arm will be organized into 5 caregivers’ peer-support platforms. A total of 12 educational sessions will be assigned to the intervention group by trained female Mbororo nutrition volunteers (n=6) and community health workers (n=6). The control arm will receive routine facility-based nutrition education. Data will be collected at 3-month and 6-month follow-up. Both descriptive statistics and multivariate logistic models will be used to estimate the effect of culturally tailored community-based nutrition education intervention (independent variable) on outcome variables (caregivers’ knowledge, attitude, and practice), child growth (weight, height/length, weight for age), and morbidity status (diarrhea, cough, and fever) between both arms. Data assessors will be blinded to the group allocation. Ethical approval (reference no. 2019/1002-07/UB/SG/IRB/FHS) was obtained from the Faculty of Health Sciences Institutional Review Board at the University of Buea.

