### Trial Design

As presented in Figure 1, this is a 2-arm parallel intervention study designed as a cluster randomized controlled trial. The randomization units will be clusters to prevent contamination between the experimental and control arms. A computer-generated list of 10 randomly selected clusters will be produced and placed in sealed, opaque envelopes.

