**Figure 1 figure1:**
[figure not shown]
Flow chart showing cluster randomization and follow-up for the nutrition, water, sanitation, and hygiene (Nu-Wash) model.

The clusters will be allocated in a 1:1 ratio in both arms. The study will be single blinded, as only the data assessors (data collectors and analysts) will be blinded to the group allocations. Within each cluster, children and caregivers meeting the inclusion criteria will be recruited for the study. Informed consent and assent will be obtained from caregivers before the intervention. Caregivers in the experimental arm will receive nutritional education under the nutrition, water, sanitation, and hygiene (Nu-WASH) model, and caregivers in the control arm will be exposed to routine nutrition education offered by health staff in the study area. Data will be collected at 3-month and 6-month follow-up.

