#### Step 2: Formation of CPGs

Caregivers in the intervention arm (n=121) were organized into 5 peer-support groups of 20 to 30 members. Each group per cluster will serve as the platform for group sessions and for interactions to enhance learning.

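### The plan randomises 10 communities and promises to consider clustering, but the only tests it names would ignore clustering if run on individuals

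*Protocol article*

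**What the plan says.** The Trial Design section makes the community the unit of allocation: "The randomization units will be clusters to prevent contamination between the experimental and control arms". The Abstract gives the numbers: "The intervention and control arms will each comprise 5 clusters with 121 child–caregiver pairs". In the intervention arm each cluster has one peer-support group: "Caregivers in the intervention arm (n=121) were organized into 5 peer-support groups of 20 to 30 members".

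For the analysis, Table 1 has a method column. It lists a t test for all three primary outcomes (for example "Change in knowledge scores" for knowledge), a t test for weight and for height/length, ANOVA for the weight-for-height z score, and a risk ratio for diarrhea, fever and cough. The Data Analysis Plan repeats this: "The *t* test and analysis of variance for comparing group means will be used for primary and secondary outcome variables". For categorical data it adds: "A chi-square test will be applied to analyze the categorized variables". It also plans multivariate logistic regression for adjusted analyses and Kaplan-Meier analysis for timed variables. Intervals are two-sided 95% and significance is set at P < .05.

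The one statement on clustering comes near the end of the Data Analysis Plan: "the clustering effect will be considered in the analysis". No cluster-level summary, mixed model, GEE or robust variance is named, and neither an ICC nor a small-sample correction is given.

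**The concern.** Caregivers in one community share a setting. In the intervention arm they also share facilitators and 12 group sessions. Their outcomes may therefore be correlated, and a test that counts 242 independent pairs would overstate the information in a comparison of 5 communities with 5. P values would then be too small and intervals too narrow, and this would affect every primary outcome.

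The general promise on clustering does not settle the matter. An analyst who ran Table 1 literally, on individuals, could claim to have followed the plan. So could one who used an off-the-shelf robust standard error, which is itself unreliable with 10 clusters. The plan thus allows analyses with quite different error rates and does not say which one is primary.

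**Working it through.** **Inputs from the protocol article.** 5 clusters and 121 pairs per arm (Abstract), hence 2 × 121 = 242 pairs, which agrees with the stated total, and a mean cluster size m = 121/5 = 24.2. Two-sided level 0.05 (Data Analysis Plan). The article gives no figure for the clustering effect, so there is none to reproduce.

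**Assumption.** ICC from 0.01 to 0.10, with 0.20 shown as a more extreme case.

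**Formulas.**
- Design effect: DE = 1 + (m − 1) × ICC = 1 + 23.2 × ICC.
- True type I error of an individual-level test at nominal 5%: 2 × [1 − Φ(1.96/√DE)].
- Width of a valid 95% interval relative to the naive one: √DE × 2.306/1.96, where 2.306 is the t critical value with 10 − 2 = 8 degrees of freedom.
- P value that a naive P of .05 becomes: refer 1.96/√DE to t with 8 degrees of freedom.

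**Example, ICC 0.05.** DE = 1 + 23.2 × 0.05 = 2.16 and √DE = 1.47. Type I error = 2 × [1 − Φ(1.96/1.47)] = 18.2%. Width ratio = 1.47 × 2.306/1.96 = 1.73.

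| Assumed ICC | DE | True type I error | Interval width ratio | Naive P = .05 becomes |
|---|---|---|---|---|
| 0.01 | 1.23 | 7.7% | 1.31 | .115 |
| 0.02 | 1.46 | 10.5% | 1.42 | .144 |
| 0.05 | 2.16 | 18.2% | 1.73 | .219 |
| 0.10 | 3.32 | 28.2% | 2.14 | .313 |
| 0.20 | 5.64 | 40.9% | 2.79 | .433 |

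**Check by simulation.** 20,000 trials per ICC with no effect and 5 clusters of about 24 per arm:
- Individual-level t test: 7.7%, 10.7%, 18.2% and 28.9% rejections at ICC 0.01, 0.02, 0.05 and 0.10.
- Individual-level chi-square, at an assumed prevalence of 27% (the mean of the planning rates 0.32 and 0.22): 7.6%, 10.5%, 18.7% and 28.2%.
- Cluster-robust z test without small-sample correction: 11.4%, 11.5% and 11.8% at ICC 0.02, 0.05 and 0.10.
- t test on the 10 community means with 8 degrees of freedom: 4.8% to 5.3% throughout.

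**Which reading is natural.** Table 1 describes outcomes measured on individuals, such as percentages of children with a symptom. A plain chi-square test, Kaplan-Meier curves and logistic regression all work on individual records. The Sample Size Determination section mentions 10% nonresponse as its only adjustment, with no ICC or design effect in the text. Nothing in the article refers to community means.

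**The case against.** A reader might infer that the trial's P values and intervals will be far too optimistic, that none of the named tests can handle clustering, or that the plan contradicts itself. The article does not support these stronger readings. It commits to considering clustering in the same section that names the tests, so anticonservative results follow only if that commitment is not carried out. It never states the unit of analysis. A t test on the 10 community means is still a t test, and it holds its level. ANOVA can carry a community term, and a risk ratio is an effect measure that does not dictate how its standard error is obtained. The named tests and the promise can therefore be reconciled; what is missing is the statement that does so.

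Two further objections have some force. First, this is a condensed article, and details such as the degrees-of-freedom method are often left to an analysis plan. That excuses the missing detail. It does not excuse a method column that names standard tests which, read at face value, do not fit the design. Second, the size depends on an unknown ICC. The primary measures are changes in score, which subtract stable community differences, so their ICC may be low. At 0.01 the inflation is modest. However, communities can also differ in how much they change, and delivery through one group per intervention community gives a reason to expect some correlation in change. The article offers no ICC that would show the problem to be negligible.

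The robust z test is not something the article proposes. It is relevant only because it is a common way of considering clustering that would not be adequate here.

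**Conclusion.** The point holds in conditional form. The plan names specific tests that, applied to individuals, ignore the randomised communities, and it offsets this only with an undertaking that has no method attached. If the tests are applied to individuals, type I error would be about 8% at ICC 0.01, 10.5% at 0.02, 18% at 0.05 and 28% at 0.10, and valid intervals would be about 1.3 to 2.1 times as wide. An uncorrected robust method would give about 12%. These figures assume equal or nearly equal clusters of about 24, a common ICC in both arms and the ICC values shown, none of which comes from the article. The analysis of every primary outcome depends on this choice. The Results section reports data collection and analysis as ongoing, so the choice should be fixed before the arms are compared.

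**What to change.** In Table 1 and the Data Analysis Plan, replace the plain tests with a named primary analysis suited to 10 clusters:

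- **Continuous outcomes:** a t test on the 10 community means (baseline-adjusted where planned) with 8 degrees of freedom, or a linear mixed model with a random community intercept and Kenward-Roger or Satterthwaite degrees of freedom. Choose one as primary.
- **Binary outcomes:** a comparison of community-level risks, or GEE with small-sample-corrected standard errors and t critical values. Either can report the risk ratio that Table 1 lists.
- **Unclustered t test, ANOVA and chi-square:** keep for description only, and say so.
- **The sentence on clustering:** replace it with a reference to these methods.

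The change needs revised wording and standard software, with no new data. The downside is wider confidence intervals, which reflect what 5 communities per arm can show.

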#### Step 6: Midline and Endline Data Collection and Analysis

Data will be collected from both the intervention and control arm at 3-months and 6-month follow-up with the same data collection tools, methods, and procedures as those used at baseline.

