### Study Objectives

#### Primary Objective

The primary objective will be to investigate the impact of a Nu-WASH versus facility-based nutrition education on caregivers’ KAP regarding complementary feeding at baseline, 3-month follow-up, and 6-month follow-up. In the absence of a gold standard test in the measurement of KAP, composite measures will be used in this study. A composite knowledge score will be built on 4 measures based on 4 self-report questionnaire items. Knowledge will first be estimated by each measure and classified into 2 categories as adequate and inadequate before the results of the 4 measures are finally combined into the composite knowledge score. Similarly, composite scores for attitude and practice will comprise 10 and 7 measures, respectively, as derived from corresponding numbers of self-report questionnaire items.

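### Logistic regression is named for outcomes that Table 1 defines as continuous (caregiver scores, child growth), and the change-score t test is less precise than adjusting for the baseline score

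*Protocol article*

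**What the plan says.** Table 1 lists the three primary outcomes as ratio-scale and continuous. For knowledge the measure is "Change in knowledge scores", and attitudes and practices are treated the same way; the method for each is a t test. Weight and height/length are also continuous, measured as change and compared by t test.

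The Primary Objective section explains how the scores are built. Knowledge items are "classified into 2 categories as adequate and inadequate before the results of the 4 measures are finally combined into the composite knowledge score", and "composite scores for attitude and practice will comprise 10 and 7 measures, respectively". It gives no threshold that would turn any of the three composites into a yes/no outcome.

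The Data Analysis Plan confirms that the t test and "analysis of variance for comparing group means will be used for primary and secondary outcome variables". It then names one adjusted method: "Adjusted analyses using baseline variables will be performed using multivariate logistic regression to determine the continuing influence of key baseline characteristics on the outcomes". The abstract's Methods paragraph states that "multivariate logistic models will be used to estimate the effect of culturally tailored community-based nutrition education intervention (independent variable) on outcome variables", and the list that follows covers the caregiver scores, child growth and morbidity.

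Baseline scores and anthropometry were collected before allocation (Step 1). Follow-up is to be done "with the same data collection tools, methods, and procedures as those used at baseline".

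**The concern.** Logistic regression needs a binary or otherwise categorical response. Applied to a score that the plan calls continuous, it leaves two possibilities. Either there is no adjusted analysis of the primary outcomes, or somebody chooses a cut-off that the article does not declare, possibly after seeing the data. In the second case the result is an odds ratio for passing a threshold, which is a different quantity from the difference in mean score that Table 1 sets out to measure.

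The comparison that does suit the outcome type, a t test on change, uses the baseline score in a less efficient way than regression on it. A trial with five communities per arm has little precision to spare, and the covariate needed is already in hand.

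**Working it through.** **Step 1: outcome type against model**

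| Outcome | Type in Table 1 | Method in Table 1 | Effect model in abstract | Adjusted model in Data Analysis Plan |
|---|---|---|---|---|
| Knowledge, attitude, practice | continuous | t test on change | logistic | logistic |
| Weight, height/length | continuous | t test on change | logistic | logistic |
| Diarrhea, fever, cough | categorical | risk ratio | logistic | logistic |

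Only the last row has an outcome that a logistic model can take as it stands. For the first two rows, the abstract and Table 1 point to different effect measures.

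**Step 2: precision at individual level**

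The article gives no standard deviation, no correlation between baseline and follow-up, and no precision figure for the scores, so there is no stated figure to reproduce. Inputs:

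- 121 pairs per arm (abstract).
- Equal SD σ at baseline and follow-up (assumption).
- Correlation r between the two (assumption, shown over a range).

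With n per arm, the variance of the estimated arm difference is:

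- change score: (2σ²/n) × 2(1 − r)
- baseline-adjusted (ANCOVA): (2σ²/n) × (1 − r²)
- ratio of the second to the first: (1 − r²) / [2(1 − r)] = (1 + r)/2

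| assumed r | 2(1 − r) | 1 − r² | variance ratio | SE ratio (square root) |
|---|---|---|---|---|
| 0.3 | 1.40 | 0.91 | 0.65 | 0.81 |
| 0.5 | 1.00 | 0.75 | 0.75 | 0.87 |
| 0.7 | 0.60 | 0.51 | 0.85 | 0.92 |

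The ratio is below 1 for every r < 1. It runs from 0.55 at r = 0.1 to 0.95 at r = 0.9, so the gain is small for any outcome whose baseline and follow-up values are very highly correlated.

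**Step 3: what clustering does to this**

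A simulation used 10 communities of 24 pairs, an assumed intracluster correlation of 0.05, an assumed effect of 0.36 SD and 1,000 runs per setting.

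- *Clusters ignored.* Type I error was about 16–19% for the change-score t test and 18–19% for plain ANCOVA. Baseline adjustment does not cure clustering.
- *Cluster-level analysis.* Type I error was near 5% for both. Power for change score versus baseline-adjusted was 29% v 42% (r = 0.3), 39% v 49% (r = 0.5) and 58% v 65% (r = 0.7).

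A separate simulation with r = 0.5 (10 clusters of 24, 500 runs each) fitted a random community intercept with default Wald inference. Type I error was about 7% at an intracluster correlation of 0.05 and 10% at 0.10. A random intercept therefore needs a small-sample correction as well.

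**The case against.** The strongest case on the other side has four parts.

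- *The primary comparison is the t test, and it is sound in type.* This stands. Under randomisation a t test on change is unbiased, and both estimators were unbiased in the simulation. Its fault, clustering aside, is inefficiency.
- *The logistic sentence in the Data Analysis Plan may be meant for morbidity only.* It follows a sentence on risk ratios for binary outcomes, and its stated purpose is the influence of baseline characteristics. Taken alone it is weaker evidence. The abstract closes this reading, because it assigns logistic models to the intervention effect on the caregiver scores and growth as well.
- *The authors may intend to dichotomise the scores.* The sample size uses two proportions, 0.32 and 0.22, which could hint at this. But the article ties those proportions to no outcome, gives no cut-off, and calls the scores continuous in Table 1.
- *A statistical analysis plan may settle it.* Such a plan can add detail, but this article already names two incompatible analyses for the same outcomes.

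A reader might infer more than the article supports:

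- *That regression to the mean biases the planned comparison.* It matters for a chance baseline imbalance in one realised allocation; it is not a bias of the randomised design.
- *That the gap between baseline in September 2019 and allocation in February 2020 has lowered r.* The dates are given, but no correlation is.
- *That the variance ratio converts into a number of extra pairs.* With five communities per arm, variation between communities limits precision, so pairs added within communities are not a fair currency.
- *That a median split would discard a known share of the information.* No median split is proposed, and a knowledge score built from four adequate/inadequate items may take as few as five values, so a figure derived for a normal score does not apply.

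**Conclusion.** The mismatch is established from the text alone: the only adjusted model named, which the abstract also gives as the effect model, cannot be fitted to the primary outcomes or to weight and height as Table 1 defines them. It would not estimate a difference in score.

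The precision point is real but conditional. At individual level the adjusted analysis has 0.65, 0.75 or 0.85 of the change-score variance at r = 0.3, 0.5 or 0.7, with r and equal SDs assumed. How much of that gain survives in a trial of 10 communities depends on the intracluster correlation and the cluster-level correlation, neither of which the article states. The simulated power figures illustrate one set of assumptions and are not predictions for this trial.

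This should be corrected before the analysis. It is not fatal, because an unadjusted comparison of the right type is planned and the article says that clustering will be considered.

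**What to change.** For each continuous outcome, replace the logistic model in the abstract and the Data Analysis Plan, and the change-score t test in Table 1, with one of these:

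- a linear mixed model of the follow-up value on arm and the baseline value of the same measure, with a random community intercept and small-sample degrees of freedom (for example Kenward-Roger or Satterthwaite); or
- a baseline-adjusted cluster-level analysis.

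Report the adjusted mean difference with its 95% CI at the planned follow-up times. Keep a binary-outcome model for diarrhea, fever and cough only. If a dichotomised score is wanted as well, state its cut-off now and label it as an additional analysis.

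The cost is wording. The baseline values are already collected and no extra data are needed. The article reports no results yet, so the change can be recorded before they are known.

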#### Step 5: Monitoring and Evaluation

CNVs and CHWs will visit households once monthly to monitor compliance and encourage proper child-feeding practices, treatment, and safe storage of drinking water. Data relevant to the study will be collected during each visit with the use of structured observation forms.

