#### Secondary Objective

The secondary objective will be to compare nutrition outcomes of Mbororo children (aged 3-59 months) at baseline, 3-month follow-up, and 6-month follow-up in the control and experimental groups. Nutrition outcomes will be defined as child growth measured as length/height, weight, and weight-for-age at baseline and endline; and child morbidity status will be measured as self-reported incidence of diarrhea, fever, and cough at 2 weeks preceding baseline, and at 3-month and 6-month data collection.

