#### Secondary Outcomes

As shown in Table 1, the secondary outcomes will comprise child growth (height/length, weight, and weight-for-height), which will be measured at 6-month follow-up, and child morbidity status (diarrhea, fever, and cough 2 weeks preceding baseline), which will be self-reported.

**Table 1 table1:** Primary and secondary outcome variables among study participants at baseline, 3 months, and 6 months.

Outcome measures					Scale			Type			Measure			Analysis method

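### Kaplan-Meier analysis is assigned to child morbidity, but the protocol defines morbidity as a two-week-recall percentage at two surveys and describes no event times

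*Protocol article*

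**What the plan says.** The Data Analysis Plan gives child morbidity a time-to-event method: "The Kaplan-Meier survival analysis will be used for timed variables like morbidity". The same section also says: "Results for group comparisons will be expressed as a risk ratio for binary outcomes".

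The sections that define the outcome describe something else:

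- **Secondary Objective:** morbidity is "self-reported incidence of diarrhea, fever, and cough at 2 weeks preceding baseline, and at 3-month and 6-month data collection".
- **Secondary Outcomes:** "child morbidity status (diarrhea, fever, and cough 2 weeks preceding baseline), which will be self-reported".
- **Table 1 (child morbidity at 3 and 6 months):** each symptom is nominal and categorical. The measure is the percentage "of children with diarrhea", with matching rows for fever and cough, and the analysis is a risk ratio.
- **Step 6:** data are collected at "3-months and 6-month follow-up with the same data collection tools, methods, and procedures as those used at baseline".

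Logistic regression appears in two roles. In the Abstract (Methods) it estimates the intervention effect on outcomes that include morbidity. In the Data Analysis Plan it serves adjusted analyses of how baseline characteristics bear on the outcomes.

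**The concern.** Kaplan-Meier estimation needs, for each child, a starting time, a time of first event or of censoring, and continuous knowledge of who is still event-free. A report of whether a child was ill in a recent fortnight, taken on two occasions three months apart, supplies none of these. It supports a period prevalence at each survey, which is how Table 1 treats it. The analysis section names morbidity itself as the example, so its sentence cannot be read as meant for some other variable.

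If the sentence were followed, every event would be placed at a survey date, and illness in the unobserved weeks would count as event-free time. The resulting figure would look like time to first illness without estimating it. Keeping it beside the risk ratio also leaves two analyses open for each of three symptoms.

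The secondary issue is the scale of the adjusted effect. The declared measure is a risk ratio, but the only adjusted model named produces an odds ratio unless its results are converted.

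**Working it through.** The protocol attaches no figure to the Kaplan-Meier analysis (no event count, hazard ratio or event-driven sample size), so there is nothing to reproduce. The checks below show what the described data could support.

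**1. Share of follow-up observed.** Inputs: two follow-up surveys (Step 6) and a 14-day recall (Secondary Objective). The recall at follow-up is an inference: Secondary Outcomes ties the two weeks to baseline only and the Secondary Objective is ambiguous, but Step 6 says the baseline tools are reused. Six months is taken as 182.5 days (about 183).

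- Observed: 2 × 14 / 182.5 = 28 / 182.5 = 15.3%
- Unobserved: 100% − 15.3% = 84.7%, about 85%

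**2. What a curve from these windows would show.** The protocol gives no onset rates, so a range is assumed. Let p be the probability of an onset in 14 days, with a constant daily rate λ = −ln(1 − p)/14.

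- True six-month cumulative incidence: 1 − exp(−182.5λ)
- Children flagged in at least one window: 1 − (1 − p)². With no dropout, this is also the six-month Kaplan-Meier estimate.
- Probability that the first episode falls in a window: [exp(−77.25λ) − exp(−91.25λ)] + [exp(−168.5λ) − exp(−182.5λ)]. Dividing by the cumulative incidence gives the share of first episodes.

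Example, p = 0.10:

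- λ = 0.10536/14 = 0.00753 per day
- True incidence = 1 − exp(−1.373) = 74.7%
- Flagged = 1 − 0.81 = 19.0%
- First episode in a window = 0.084, and 0.084/0.747 gives about 11%

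| Assumed p | True six-month incidence | Flagged by the two windows | Share of first episodes inside a window |
|---|---|---|---|
| 0.05 | 48.8% | 9.8% | 13.3% |
| 0.10 | 74.7% | 19.0% | 11.3% |
| 0.20 | 94.5% | 36.0% | 7.6% |
| 0.30 | 99.0% | 51.0% | 4.6% |

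Across the range, the curve would fall far short of the quantity it appears to show. Interval-censored methods would not repair this, because an illness-free fortnight before the 3-month survey says nothing about the weeks before that fortnight.

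**3. Odds ratio against risk ratio.** Assumed: control prevalence 30% or 40%, true risk ratio 0.70. These are unadjusted conversions and show scale only.

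- 30%: intervention prevalence 0.70 × 0.30 = 0.21; OR = (0.21/0.79)/(0.30/0.70) = 0.266/0.429 = 0.62
- 40%: intervention prevalence 0.70 × 0.40 = 0.28; OR = (0.28/0.72)/(0.40/0.60) = 0.389/0.667 = 0.58

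The odds ratio lies further from 1. Read as a risk ratio, it would turn a 30% reduction into 38-42%.

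**The case against.** **Onset dates may exist.** The questionnaire is not shown, and Caregivers' Interviews says only that it covers the child's health status. Step 5 also provides monthly contact: "CNVs and CHWs will visit households once monthly to monitor compliance and encourage proper child-feeding practices, treatment, and safe storage of drinking water", and "Data relevant to the study will be collected during each visit with the use of structured observation forms". A reader might infer that no event times exist at all. The documents do not support that; they support only that none are described. The 85% figure likewise assumes the surveys are the sole morbidity source. The monthly visits do not remove the problem, however. Their stated purpose is compliance and encouragement, and no morbidity dating is mentioned. They are made by the people who deliver the intervention, six volunteers and six health workers against ten clusters. Comparable dating in the control arm is therefore not established.

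**Several effect measures are not a contradiction in themselves.** A reader might infer that the survival curve, risk ratio and odds ratio are three incompatible estimands. That goes too far. A risk ratio and an odds ratio are two measures of one binary outcome, reporting both is common, and a risk ratio can be obtained from a logistic model by standardisation. The Data Analysis Plan also words the logistic model as concerning baseline characteristics. What stands is narrower: the Abstract uses that model for the intervention effect, so the scale of the adjusted result must be stated.

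**Impact is limited.** Morbidity is secondary, and Table 1 already lists a suitable analysis. This is correct and bounds the weight of the point.

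**Conclusion.** The point holds as an internal conflict. The analysis section treats morbidity as time-to-event data, while the objective, the outcome section and Table 1 define a categorical, short-recall outcome at fixed surveys. As written, the Kaplan-Meier rule does not fit the data described.

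The 85% unobserved follow-up rests on a two-week recall at both follow-up surveys and no other morbidity source. The incidence table rests on assumed constant onset rates and shows direction and order of size only. That the outcome is binary is read from Table 1's classification and percentage measure; the protocol does not say yes/no.

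The odds-ratio matter is secondary and rests on assumed prevalences and an assumed effect. No sample size, power figure or primary conclusion is affected. The correction should be made, but it does not threaten the trial.

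**What to change.** 1. In the Data Analysis Plan, delete the Kaplan-Meier sentence for morbidity. If onset dates are in fact collected by the same method in both arms, the protocol would have to say so and define the time origin, the event and censoring before any survival analysis is planned.
2. In the Secondary Objective, replace incidence with two-week period prevalence, and state in Secondary Outcomes that the two-week recall applies at the 3- and 6-month surveys as well as at baseline.
3. Analyse each symptom at 3 and 6 months by the risk ratio already in Table 1, allowing for clustering as the Data Analysis Plan already undertakes to do.
4. Report the adjusted intervention effect as a risk ratio, for example from a log-link model or by standardisation from the logistic model, or label it clearly as an odds ratio.

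The cost is wording only. No new data are needed and the sample size does not change.
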